### Data analysis

For the TXA primary efficacy outcome, we will analyze patients in the treatment group to which they are allocated, according to the intention-to-treat principle. We will conservatively test the non-inferiority safety hypothesis in the per-protocol population [39]; a sensitivity intention-to-treat analysis will be secondarily performed. The analyses of the primary outcome in the BP management factorial will follow the intention-to-treat principle. Patients lost to follow-up will be censored at the time of their last follow-up. We will develop and finalize a statistical analysis plan before any investigator is unblinded.

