### Trial interventions

#### Tranexamic acid or placebo

Patients receive two intravenous doses of either 1 g of TXA or matching placebo (i.e., equivalent volume of 0.9% normal saline), as a bolus or 10-min infusion. The first dose is given at the beginning of surgery (i.e., within 20 min preceding the anticipated skin incision), and the second at the end of surgery (i.e., at wound closure). Additional File 3 provides the rationale for the choice of the TXA dosing regimen in this study.

TXA and 0.9% normal saline are sourced locally. Centers use any approved marketed version of TXA 100 mg/mL solution. The study drugs are prepared either by a pharmacist or another designated qualified personnel, who are not involved in any other study activities. In order to ensure blinding, individuals preparing study drugs at each participating center sign an agreement indicating they will maintain the confidentiality of randomization assignments.

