### Statistical considerations

#### Sample size

The hypothesis of non-inferiority of TXA on thrombotic events compared with placebo is the one requiring the largest sample size. Table 3 shows the related sample size calculations. We expect the placebo event rate for the composite of arterial and venous thrombotic events to range between 10 and 12% (after accounting for the partial factorial design). We set up the non-inferiority margin on a hazard ratio (HR) with TXA compared with placebo of 1.125, which, given the expected placebo event rates, correspond to an absolute increase between 1.18 and 1.39%. The relative 12.5% hazard increase as non-inferiority margin was chosen to be half the 25% relative hazard reduction used to establish the superiority of either aspirin or clonidine compared with placebo in POISE-2 [5, 26]. Although we designed POISE-3 to establish if TXA is non-inferior to placebo, it is possible that TXA might in fact have a small beneficial effect on postoperative cardiovascular events due to the decreased bleeding. We quantified this small beneficial effect to correspond to a true HR of 0.9 (Table 3). Based on these assumptions, a sample size of 10,000 patients will allow us to test our non-inferiority hypothesis, with a power of ≥ 90% (Table 3).

**Table 3 Tab3:** Sample size calculation for non-inferiority safety hypothesis of tranexamic acid vs. placebo

Placebo event rate	NI margin, absolute risk difference TXA vs. placebo^**b**^	Power	Sample size^**c**^
		0.90	8,868
**10%**^**a**^	1.18%	0.95	10,963
		0.97	12,441
		0.90	8,078
**11%**^**a**^	1.29%	0.95	9,990
		0.97	11,340
		0.90	7,390
**12%**^**a**^	1.39%	0.95	9,136
		0.97	10,367

*NI* non-inferiority margin, *TXA* tranexamic acid

^a^The estimates are based on the event rates observed in the POISE-2 trial (aspirin-placebo group) [5] and in a simulated subpopulation of the VISION cohort [1, 2] matching the POISE-3 inclusion criteria

^b^These are the NI margins expressed as absolute risk differences, corresponding to a NI margin expressed as hazard ratio of 1.125, when the placebo event rate is 10%, 11%, or 12%

^c^These sample sizes are obtained from non-inferiority test for two survival curves using Cox’s proportional hazard model, with a hazard ratio of 1.125 as non-inferiority margin, and a hazard ratio of 0.9 as actual hazard ratio (one-sided test, alpha of 0.025)

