#### Main analysis

For the analyses on each primary outcome, we will use Cox proportional hazards models with stratification according to the randomization in the partial factorial. We will assess model assumptions including the proportional hazard assumption. We will present the time-to-the first occurrence of one of the components of the primary outcomes using the Kaplan-Meier estimator.

For the effect of TXA on the primary safety outcome, we will calculate the HR and the corresponding upper bound of the one-sided 97.5% CI. We will declare the non-inferiority of TXA compared with placebo if the upper bound falls below 1.125.

For the effect of TXA compared with placebo on the primary efficacy outcome, and the effect of the hypotension-avoidance strategy compared with the hypertension-avoidance strategy on the primary outcome, we will calculate the HRs, corresponding 95% CIs and associated p-values. We will infer statistical significance if the computed 2-sided *p*-value is < 0.05. A similar approach will be adopted for the secondary and tertiary outcomes.

We anticipate that the effect of TXA and of the hypotension-avoidance strategy will act independently, but we will evaluate the possibility of synergism or antagonism between the two interventions by formally testing for differences among the strata.

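### Non-inferiority on thrombotic safety is decided from the per-protocol population only and called conservative, while the planned intention-to-treat analysis has no part in the decision

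*Protocol article*

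**What the plan says.** The Data analysis section of the Protocol article assigns populations to the three primary analyses. TXA efficacy and the blood pressure outcome follow intention-to-treat. The TXA safety outcome does not: "We will conservatively test the non-inferiority safety hypothesis in the per-protocol population [39]; a sensitivity intention-to-treat analysis will be secondarily performed".

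The Main analysis section gives the rule for the HR and its one-sided 97.5% bound: "We will declare the non-inferiority of TXA compared with placebo if the upper bound falls below 1.125". It names no second population and attaches no condition about the intention-to-treat result.

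The Sample size section fixes the design values: "We set up the non-inferiority margin on a hazard ratio (HR) with TXA compared with placebo of 1.125", "a hazard ratio of 0.9 as actual hazard ratio", and "one-sided test, alpha of 0.025". The placebo rate is expected "to range between 10 and 12% (after accounting for the partial factorial design"). This hypothesis needs the largest sample of those in the trial, and the section states power of at least 90% with 10,000 patients.

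Three other statements bear on the point. Allocation to TXA or placebo is blinded to all parties (Randomization and blinding). Outcome data are still collected after a deviation from the intervention (Follow-up). A statistical analysis plan is to be finalised before any investigator is unblinded (Data analysis).

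**The concern.** The usual reason to prefer per-protocol in a non-inferiority trial is sound. Non-adherence pulls the intention-to-treat HR towards 1 and makes non-inferiority easier to show. That reason covers only one route to a false claim. The per-protocol set is chosen on what happened after randomisation, so the arms compared are no longer the randomised arms. If exclusions are related to outcome and differ between arms, the HR can move in either direction.

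At stake is the trial's main safety conclusion, which is the one primary decision taken off the randomised set. If the two analyses disagree, the rule as written declares non-inferiority from the per-protocol bound even when the intention-to-treat bound lies above 1.125. The discordant result would be reported but would not change the declaration. This is a stated choice and not a detail left out: defining the per-protocol set elsewhere would not by itself give intention-to-treat a role.

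**Working it through.** **Inputs from the Protocol article.** Margin HR 1.125, true HR 0.9, one-sided alpha 0.025, placebo rate *p* of 10% to 12%, 10,000 patients at 1:1 (5,000 per arm).

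**Assumed, because the article gives no figure.** The share of patients excluded from the per-protocol set, and the number of event patients lost in each arm.

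**1. The plan's own figures.** Events needed: D = 4(z₀.₉₇₅ + z_power)² / ln(1.125/0.9)². Total N = D / mean risk, with TXA risk 1 − (1 − p)^0.9.
- For 90% power, D = 844.1.
- At p = 10% the TXA risk is 9.05% and the mean risk 9.52%, so N = 8,864 (Table 3: 8,868).
- At 11% and 95% power, N = 9,963 (Table 3: 9,990).
- At 12% and 97% power, N = 10,365 (Table 3: 10,367).
- All nine sizes agree within 0.3%. The absolute margins 1 − (1 − p)^1.125 − p come to 1.18%, 1.29% and 1.39%, as stated.
- Power at N = 10,000 is 93.1%, 95.1% and 96.5% for p = 10%, 11% and 12%.

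No stated figure is wrong.

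**2. Sensitivity of the per-protocol decision (hypothetical).** Take p = 11% and true HR 1.125. TXA risk is 1 − 0.89^1.125 = 12.287%, or 614.4 expected events against 550 on placebo. Remove k₁ TXA and k₀ placebo event patients:
- q₁ = (614.4 − k₁)/(5,000 − k₁) and q₀ = (550 − k₀)/(5,000 − k₀)
- HR = ln(1 − q₁)/ln(1 − q₀)
- P(declare) = Φ[ln(1.125/HR)·√E/2 − 1.96], where E is the total of remaining events

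| TXA lost | Placebo lost | Per-protocol HR | False non-inferiority |
|---|---|---|---|
| 0 | 0 | 1.125 | 2.5% |
| 10 | 0 | 1.108 | 4.5% |
| 15 | 0 | 1.099 | 5.9% |
| 25 | 0 | 1.082 | 9.6% |
| 15 | 10 | 1.118 | 3.1% |
| 25 | 15 | 1.111 | 4.1% |
| 10 | about 9 | 1.125 | 2.5% |

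The last row removes events in proportion to the number in each arm (10 × 550/614.4 ≈ 9).

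**3. A discordant result.** Suppose the observed intention-to-treat HR is 1.02 at p = 11%, with 560.4 and 550 events. The standard error is √(1/560.4 + 1/550) = 0.060 and the upper bound is 1.02 × e^(1.96 × 0.060) = 1.147, so non-inferiority fails. Removing 12 TXA event patients only gives HR 0.999 and a bound of 1.1249, and the rule declares non-inferiority. Across placebo rates of 12% to 10% the intention-to-treat bound is 1.142 to 1.154, and 10 to 14 such losses are enough.

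**4. The opposite direction.** At true HR 0.9, removing 5% of placebo events only lowers power from 93.0% to 75.6% at p = 10%, and from 95.0% to 79.6% at p = 11%. The direction of bias is not fixed.

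**5. Power if both populations must pass.** True HR 0.9, N = 10,000, share x excluded without relation to outcome, and a bivariate normal with correlation √(1 − x):

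| Placebo rate | Intention-to-treat alone | Per-protocol alone, x = 5% | Both, x = 2% | Both, x = 5% | Both, x = 10% |
|---|---|---|---|---|---|
| 10% | 93.1% | 91.9% | 92.1% | 91.1% | 89.6% |
| 11% | 95.1% | 94.1% | 94.3% | 93.5% | 92.2% |
| 12% | 96.5% | 95.7% | 95.9% | 95.3% | 94.2% |

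When intention-to-treat must also pass, the false non-inferiority rate cannot exceed that of the intention-to-treat test, 2.5% when the intention-to-treat HR is 1.125.

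**The case against.** Per-protocol as the primary set, with intention-to-treat as sensitivity, is a prespecified choice supported by a citation, and avoiding dilution is a legitimate reason for it. Intention-to-treat is planned and feasible, so a disagreement would be visible to readers. Blinding prevents exclusions made in knowledge of the arm. The one-arm scenarios are extreme: at HR 1.125 the whole 30-day excess is about 64 events (614.4 − 550), so 10 to 25 TXA-only losses amount to 16% to 39% of it with no placebo counterpart. All of this stands, and it limits the size of the problem. It does not make a post-randomisation subset conservative, and it does not give the randomised comparison a role in the decision.

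A reader might go further. The second dose comes late ("and the second at the end of surgery (i.e., at wound closure"), so a patient with an intraoperative event might miss it and leave the per-protocol set together with the event. The documents do not support stating this as what will happen:
- The article does not define the per-protocol population. Whether both doses are required is not shown, and that definition may properly sit in the analysis plan.
- Only events before wound closure could stop the second dose, while the outcome runs to 30 days.
- Death and cardiac arrest, the most obvious reasons to miss a dose, are not components of the TXA safety composite.

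Event-driven exclusion is therefore a possibility and not a finding. No change to the per-protocol definition can be asked for on this evidence.

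**Conclusion.** The point holds in a limited form. The article rests the non-inferiority declaration on a single per-protocol bound, calls this conservative, and leaves intention-to-treat outside the rule. The label is not justified by construction, and the rule can declare non-inferiority when the randomised comparison fails 1.125.

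The size is uncertain because it depends on exclusions that the article does not describe. The range from 4.5% to 9.6% is a worst case with losses in one arm only. With losses in both arms the rate is nearer 3% to 4% in the cases worked, with proportional losses it stays at 2.5%, and bias against TXA is equally possible. These figures show that a differential loss of about a dozen events matters. They do not predict that it will occur. The point is best treated as a cheap improvement to the decision rule and not as an error in the plan's figures.

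**What to change.** In Data analysis and Main analysis, state that non-inferiority is declared only if the upper bound of the one-sided 97.5% interval is below 1.125 in both the intention-to-treat and the per-protocol populations. Delete 'conservatively', or give the reason why it applies to this outcome.

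The change is to wording only. Both analyses are already planned, outcomes are collected after deviations, and no further patients are needed. It can be made without knowledge of results if it is fixed before unblinding.

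The cost is a small loss of power: under one percentage point against per-protocol alone with an assumed 5% excluded (for example 93.5% against 94.1% at an 11% placebo rate). In the least favourable case worked, with 10% excluded at a 10% placebo rate, joint power is 89.6%, just under the stated 90%; per-protocol alone would give 90.4% there.

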#### Main analysis

For the analyses on each primary outcome, we will use Cox proportional hazards models with stratification according to the randomization in the partial factorial. We will assess model assumptions including the proportional hazard assumption. We will present the time-to-the first occurrence of one of the components of the primary outcomes using the Kaplan-Meier estimator.

For the effect of TXA on the primary safety outcome, we will calculate the HR and the corresponding upper bound of the one-sided 97.5% CI. We will declare the non-inferiority of TXA compared with placebo if the upper bound falls below 1.125.

For the effect of TXA compared with placebo on the primary efficacy outcome, and the effect of the hypotension-avoidance strategy compared with the hypertension-avoidance strategy on the primary outcome, we will calculate the HRs, corresponding 95% CIs and associated p-values. We will infer statistical significance if the computed 2-sided *p*-value is < 0.05. A similar approach will be adopted for the secondary and tertiary outcomes.

We anticipate that the effect of TXA and of the hypotension-avoidance strategy will act independently, but we will evaluate the possibility of synergism or antagonism between the two interventions by formally testing for differences among the strata.

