### Randomization and blinding

Figure 1 shows the trial flow chart. Study personnel randomize patients before surgery via a central 24-h Interactive Web Randomization System. The randomization process uses block randomization stratified by center, with block size varying randomly, and the study personnel do not know the block sizes. Patients are randomized to receive TXA or placebo according to a 1:1 ratio. Patients eligible for the BP management factorial are also randomized to the hypotension-avoidance or hypertension-avoidance strategy, with a 1:1 ratio.

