## Trial progress

This paper is based on the most recent version of the study protocol (i.e., v7.0, 2021-07-22). The first patient was randomized on June 27, 2018. The DMC undertook the planned interim analyses and recommended continuation of the trial. This study protocol was submitted when recruitment in the study was completed but before completion of last patient/last visit. A few protocol amendments have been implemented during the course of the trial with the most recent version of the protocol here reported being formally finalized close to the end of the recruitment. There was consensus among the POISE-3 investigators to publish the study protocol before closure of the study database but only in its definitive version, i.e., the one that will inform the report of the study results. Recruitment has involved 106 centers across 22 countries.

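### Randomization is blocked within center, but the primary Cox models as stated carry no center term, so the superiority tests are slightly conservative if risk differs between centers (minor)

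*Protocol article*

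**What the plan says.** Randomization and blinding section: "The randomization process uses block randomization stratified by center, with block size varying randomly". The same section gives the allocation ratio: "Patients are randomized to receive TXA or placebo according to a 1:1 ratio". Patients eligible for the blood pressure comparison are also allocated 1:1 to the two strategies. Center is the only stratification factor named.

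Main analysis section, for each primary outcome: "we will use Cox proportional hazards models with stratification according to the randomization in the partial factorial". I read this as strata for the other half of the factorial: blood pressure arm or non-participation for the tranexamic acid (TXA) models, and TXA or placebo for the blood pressure model. Center does not appear, and no reason is given.

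Trial progress section: "Recruitment has involved 106 centers across 22 countries".

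The Data analysis section says that a statistical analysis plan will be finalized before any investigator is unblinded. That plan is not at hand.

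**The concern.** When allocation is balanced within center and outcome risk varies by center, the treatment contrast is less variable than a center-free model assumes. The model standard error is then too large. Superiority tests reject less often than their nominal level under the null and lose some power under the alternative. Leaving a prognostic factor out of a Cox model also moves the estimated hazard ratio (HR) slightly toward 1.

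Variation between centers is plausible here. There are many centers in many countries, almost any noncardiac surgery qualifies, and exclusion of low-risk procedures is left to the physician's judgment. Its size is not stated anywhere. At stake is a small loss of efficiency in the TXA efficacy and blood pressure comparisons, which can be avoided without new data.

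**Working it through.** **1. The plan's own figures, which contain no center term.**

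Inputs from the Sample size section: "We expect the placebo event rate for the composite of arterial and venous thrombotic events to range between 10 and 12" per cent; margin HR 1.125; "a hazard ratio of 0.9 as actual hazard ratio (one-sided test, alpha of 0.025").

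Events needed: D = (z₀.₉₇₅ + z_power)² / [0.25 × ln(0.9/1.125)²]. For 95% power, D = (1.960 + 1.645)² / (0.25 × 0.0498) = 1,043.9.

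At an 11% placebo rate, the TXA rate is 1 − 0.89^0.9 = 9.96% and the mean is 10.48%. N = 1,043.9 / 0.1048 = 9,962, against 9,990 in Table 3. All nine entries of Table 3 reproduce within 0.4%. At N = 10,000 the power is 93.1%, 95.1% and 96.5% for placebo rates of 10%, 11% and 12%. This agrees with the statement that "a sample size of 10,000 patients will allow us to test our non-inferiority hypothesis, with a power of ≥ 90" per cent.

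Blood pressure comparison, N = 6,500, control rate 11%:
- HR 0.75: mean event rate (0.1100 + 0.0837)/2, D = 629.5, power 95.0% (stated 95%).
- HR 0.80: D = 646.8, power 81.0% (stated above 80%).

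**2. Effect of leaving center out, by simulation.**

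From the documents: 106 centers, 1:1 allocation blocked within center, 65% of patients in the blood pressure comparison, and the rates and HRs above. Assumed: uneven log-normal center sizes, small permuted blocks, and a between-center log-hazard SD of 0 to 0.8. For scale, centers one SD above and one SD below the mean differ in hazard by a factor of exp(1.0) = 2.7 at SD 0.5 and exp(1.6) = 5.0 at SD 0.8.

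Power of the blood pressure comparison:

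| SD | True HR | Factorial strata only | Center strata only |
|---|---|---|---|
| 0 | 0.80 | 79.3% | 79.1% |
| 0.5 | 0.80 | 80.3% | 80.9% |
| 0.8 | 0.80 | 79.1% | 81.1% |
| 0 | 0.75 | 94.7% | 94.7% |
| 0.5 | 0.75 | 92.9% | 93.7% |
| 0.8 | 0.75 | 94.1% | 95.1% |

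A separate simulation at SD 0.8 and HR 0.80 (1,500 runs) gave 77.7% without center and 79.7% with it. Only comparisons along a row are informative. The realized event rate drifts down as the SD rises (9.68% at SD 0 to 9.37% at SD 0.8 for HR 0.75).

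Calibration under the null at SD 0.8, blood pressure comparison (2,000 runs):
- Without center, the mean model SE is 0.0769 against an empirical SD of 0.0739. The ratio is 1.04, and two-sided rejection is 4.2%.
- With center strata, the figures are 0.0770 and 0.0768. The ratio is 1.00, and rejection is 5.1%.
- Monte Carlo error is √(0.05 × 0.95/2,000) = 0.5 points.

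For TXA efficacy at SD 0.8, null rejection is 4.7% without center and 5.3% with center strata.

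**3. Non-inferiority test at true HR 1.125** (one-sided, nominal 2.5%, 2,500 runs):

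| SD | Factorial strata only | Factorial × center | Center strata only |
|---|---|---|---|
| 0 | 2.4% | 2.5% | 2.5% |
| 0.5 | 2.8% | 2.8% | 2.8% |
| 0.8 | 2.2% | 2.3% | 2.2% |

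At SD 0.8 the average HR is 1.120 without center and 1.126 with it, so it does move toward 1. The model SE without center is 0.0604 against an empirical SD of 0.0576 (ratio 1.05), which pushes the upper bound the other way. The two effects roughly cancel.

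**4. Cost of fully crossed strata.** Three factorial groups × 106 centers gives up to 318 strata. About 10,000 × 0.1048 = 1,048 safety events then leave roughly 3.3 per stratum. At SD 0 the SE rises from 0.0620 to 0.0627, an information loss of 1 − (0.0620/0.0627)² = 2.2%. Center strata alone leave it at 0.0620.

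**The case against.** The strongest reply is that the article does not exclude center, and a separate analysis plan could add it. This stands in part: that center will be absent from the final analysis is an inference. But the article is not silent on the model. It names the strata, and it describes itself as the definitive version that will inform the report of results.

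The second reply is that the shift in HR is a change of estimand. Table 3 converts the margin using overall event rates: at 10%, 1 − 0.90^1.125 = 11.18%, a difference of 1.18 points, with no center term. A center-free HR fits that conversion. This stands as a reason not to call the shift an error, and as a reason to keep the center-free model in view.

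The third reply is that leaving center out with 106 sites is defensible, since the loss is on the conservative side and strata that are too fine cost information. This also stands. It limits the point to a minor one and shapes the remedy.

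Three stronger readings are tempting, and the documents support none of them:
- **Non-inferiority could be declared too easily because the HR is pulled toward 1.** The simulated one-sided error is no higher without center than with it.
- **The center stratification is wasted.** Balance within centers is achieved at allocation and is kept whatever model is fitted.
- **The claim of more than 80% power at HR 0.80 is wrong.** The formula gives 81.0%. The simulation gave 79.3% even at SD 0, where center cannot matter, so a figure just under 80% cannot be put down to the missing center term.

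**Conclusion.** The point holds as a minor one. Allocation is blocked within center, and the primary Cox models as stated do not reflect that. If center risks differ, standard errors are about 4 to 5% too wide at SD 0.8 and the superiority tests are slightly conservative. The cost in the blood pressure comparison at SD 0.8 is about 2 power points at HR 0.80 and about 1 point at HR 0.75. It is under 1 point at SD 0.5, and there is no loss at SD 0. Differences below a point are within simulation error.

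These sizes rest on an assumed center SD, assumed center sizes and assumed block sizes. Validity is not threatened, and the stated sample sizes and powers are reproduced without any center adjustment.

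**What to change.** State in the analysis plan, before unblinding, how center enters the primary Cox models. Either of two forms would do:
- keep the factorial strata and add center as a shared-frailty term; or
- stratify by center, pooling small centers within country by a rule based on enrolment, not on events, and fixed before unblinding.

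Do not cross factorial group with center in full. Keep the center-free model as a sensitivity analysis, and say that its HR is averaged over centers while the primary one is conditional on center.

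The cost is a sentence in the plan and a small change in the code, with no new data. Center strata cost essentially nothing in the simulations at SD 0. The frailty and pooled versions were not themselves simulated, so their gain is expected to be similar but has not been measured.

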Taking into account information from the POISE-2 trial [5], we expect a placebo event rate for the TXA primary efficacy outcome of at least 7%. With a similar placebo event rate, a sample size of 10,000 patients will give us ≥ 95% power to show a relative hazard reduction of at least 30% (i.e., HR 0.70) with TXA compared to placebo in the composite of life-threatening, major and critical organ bleeding (based on Cox’s proportional hazard model, with type I error of 0.05, two-sided test). The trial will still have 90% power to detect a relative hazard reduction of at least 25% (i.e., HR 0.75).

We expect that at least 80% of patients will be on chronic antihypertensive therapy. We conservatively estimated that at least 65% of the patients in the TXA component of the trial would be eligible for the BP management factorial. A sample of 6500 patients will provide 95% power to test the hypothesis that the hypotension-avoidance strategy will reduce the occurrence of the composite of vascular death and nonfatal MINS, stroke, and cardiac arrest with an HR of 0.75 and an expected control event rate of 11.0% (based on Cox’s proportional hazard model, type I error of 0.05, two-sided test). The same sample size will still provide > 80% power to detect a HR of 0.80.

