#### Subgroup analyses

For the primary efficacy and safety outcomes in the TXA factorial, we will evaluate the following subgroups: orthopedic versus non-orthopedic surgery; preoperative hemoglobin < 120 g/L versus ≥ 120 g/L; preoperative estimated glomerular filtration rate (eGFR) < 45, 45– < 60, and ≥ 60 ml min^−1^ 1.73 m^2^; and preoperative N-terminal pro–B-type natriuretic peptide (NT-proBNP) < 200, 200– < 1500, and ≥ 1500 ng/L. We expect TXA to have greater benefit and safety in patients having orthopedic surgery, with a preoperative hemoglobin < 120 g/L, a lower preoperative eGFR, and higher preoperative NT-proBNP values.

For the primary outcome in the BP management factorial, we will evaluate the following subgroups: chronic ACEI/ARB therapy versus no chronic ACEI/ARB therapy; number of chronic antihypertensive medications (1 versus ≥ 2); preoperative systolic blood pressure (SBP) < 130, 130–159, 160–180, and > 180 mmHg; and preoperative NT-proBNP < 200, 200– < 1500, and ≥ 1500 ng/L. We expect the hypotension-avoidance strategy will have a greater beneficial effect in patients on chronic ACEI/ARB therapy, taking ≥ 2 chronic antihypertensive medications, with a lower preoperative SBP, and higher preoperative NT-proBNP values.

For each subgroup analysis, we will undertake a Cox proportional hazards model assessing each primary outcome incorporating a subgroup interaction term to provide the basis for evaluating subgroup effects. We will consider the possibility that a subgroup effect is present if the interaction term of treatment and subgroup is statistically significant at a *p*-value < 0.05. We will also consider other credibility criteria to judge the reliability of a subgroup effect [40, 41].

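### Pre-specified adjustment of the primary Cox models for baseline predictors the trial already records would be a cheap gain in power, worth having mainly in the blood pressure comparison

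*Protocol article*

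**What the plan says.** Under Main analysis, the protocol article states one model for each primary outcome: "we will use Cox proportional hazards models with stratification according to the randomization in the partial factorial". No baseline predictor is named. For the two superiority comparisons (TXA on bleeding, BP strategy on cardiovascular events) the decision rule is "We will infer statistical significance if the computed 2-sided" *p*-value is below 0.05.

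The same article uses several baseline variables elsewhere. Its inclusion criteria (Table 1) cover coronary and peripheral arterial disease, stroke, transient ischemic attack, age and type of surgery. Its exclusion criteria (Table 2) require a Cockcroft-Gault creatinine clearance. Subgroup analyses lists "orthopedic versus non-orthopedic surgery", preoperative hemoglobin, eGFR and NT-proBNP, but only as interaction factors. Randomization is stratified by center alone.

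Sample size bases power on a Cox model "with type I error of 0.05, two-sided test" and mentions no adjustment. For the BP comparison with 6,500 patients and an 11.0% control rate it gives 95% power at HR 0.75, and adds: "The same sample size will still provide > 80% power to detect a HR of 0.80". For TXA, "we expect a placebo event rate for the TXA primary efficacy outcome of at least 7"%, "a sample size of 10,000 patients will give us ≥ 95% power to show a relative hazard reduction of at least 30"%, and "The trial will still have 90% power to detect a relative hazard reduction of at least 25"%.

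**The concern.** When a predictor of the outcome is left out of a Cox model, the estimated treatment HR lies closer to 1 than the HR among patients with the same baseline risk. The test then has less power than one that conditions on the predictor. If the listed variables predict bleeding and cardiovascular events at all well, the stated model gives up power that could be had without new data.

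The BP comparison has least to spare, at just over 80% power in its second scenario. According to Trial progress, recruitment was complete when the article was submitted. The sample size could no longer be raised, while the analysis could still be specified before unblinding.

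**Working it through.** **Inputs from the article (Sample size; Randomization and blinding).** BP: 6,500 patients, control rate 11.0%, HR 0.75 or 0.80. TXA bleeding: 10,000 patients, placebo rate 7%, HR 0.70 or 0.75. Allocation 1:1, two-sided 0.05. No dropout rate is given, so none is applied.

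**Step 1: reproduce the stated power.** With control risk p_c, the treated risk is p_t = 1 − (1 − p_c)^HR. Expected events are E = (N/2)(p_c + p_t). Power (Schoenfeld) is Φ(½√E · |ln HR| − 1.96).

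- BP, HR 0.80: p_t = 1 − 0.89^0.80 = 0.0890; E = 3,250 × 0.1990 = 647; ½√647 × 0.2231 − 1.96 = 0.878; power 81.0% (stated: above 80%).
- BP, HR 0.75: p_t = 0.0837; E = 629; power 95.0% (stated: 95%).
- TXA, HR 0.70: p_t = 0.0495; E = 598; power 99.2% (stated: at least 95%).
- TXA, HR 0.75: p_t = 0.0530; E = 615; power 94.6% (stated: 90%, so the article is on the conservative side).

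The plan and its power figures are therefore consistent with an unadjusted model.

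**Step 2: add a prognostic score.** The documents give no prognostic strength, so a C-index is assumed. A normally distributed score has standard deviation √2 · Φ⁻¹(C), that is 0.36, 0.55, 0.74 and 0.95 for C = 0.60, 0.65, 0.70 and 0.75. The planned HR is taken as marginal (unadjusted). The conditional HR that gives the same 30-day risks in both arms is found by numerical integration over the score. It then goes into the Step 1 power formula with the same E.

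| Comparison | Unadjusted power | C = 0.60 | C = 0.65 | C = 0.70 | C = 0.75 |
|---|---|---|---|---|---|
| BP, HR 0.80: conditional HR | – | 0.799 | 0.797 | 0.794 | 0.788 |
| BP, HR 0.80: power | 81.0% | 81.5% | 82.3% | 83.6% | 85.7% |
| BP, HR 0.75: conditional HR | – | 0.749 | 0.746 | 0.743 | 0.736 |
| BP, HR 0.75: power | 95.0% | 95.3% | 95.6% | 96.2% | 97.0% |
| TXA, HR 0.75: power | 94.6% | 94.8% | 95.0% | 95.4% | 96.1% |
| TXA, HR 0.70: power | 99.2% | 99.2% | 99.3% | 99.4% | 99.5% |

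The equivalent gain in events is (ln HR_cond / ln HR)² − 1. For BP at HR 0.80 that is 3.6%, 7.3% and 13.7% at C = 0.65, 0.70 and 0.75, or about 230, 470 and 890 of 6,500 patients.

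**Step 3: simulation check.** In 1,000 simulated trials per setting for BP at HR 0.80, the share of significant results without and with adjustment was 79.9% and 81.0% (C = 0.65), 78.6% and 82.1% (C = 0.70), and 81.2% and 86.7% (C = 0.75). The standard error of the log HR was 0.0792 in both models each time. At C = 0.75 the mean HR moved from 0.798 to 0.786. All of the gain comes from the shift in the HR and none from a smaller standard error.

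**Step 4: the other reading of the planned HR.** If 0.80 is taken as conditional, a separate simulation (score SD 0.6, 0.8 and 1.0) puts BP power at 80.0%, 77.4% and 74.7% unadjusted, against 81.8%, 80.7% and 80.3% adjusted. The gap between the models is 1.8, 3.3 and 5.6 points. Under this reading adjustment protects the stated power and does not raise it.

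**The case against.** The strongest reply is that nothing here is wrong. The stated model gives a valid test, matches the basis of the sample size, and reproduces the BP figures. That stands, and it makes this an improvement rather than a defect.

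A second reply is that covariate lists belong in the statistical analysis plan, which the article says is still to be finalized and which is not shown. The article does not rule out adjustment. But it does state the model for each primary outcome, and Trial progress describes the published version as the definitive one. The point concerns a choice that is stated, not a missing detail.

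Four stronger readings are tempting, and the documents do not support them:

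- *The plan loses precision.* It does not: the standard error is the same with and without adjustment. What changes is the quantity estimated, from a marginal to a conditional HR.
- *The loss buys nothing.* The unadjusted model keeps the marginal HR behind the sample size and needs no covariate data. NT-proBNP is one of six entry routes, and the article does not say that it is measured in everyone.
- *Both superiority tests suffer materially.* TXA bleeding already has 94.6% to 99.2% power. Only BP at HR 0.80, which is the second scenario and not the design target, gains noticeably.
- *Chance imbalance threatens the result.* With 6,500 to 10,000 patients it should be small, and the unadjusted test already allows for it.

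There is also a fair objection to the remedy. The TXA efficacy result would rest on a conditional HR and the safety decision on an unadjusted one. Reporting the unadjusted efficacy HR alongside largely answers this.

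**Conclusion.** The point holds as a cheap improvement centred on the BP comparison. For an assumed C-index of 0.65 to 0.75, the gain is about 1.3 to 4.7 points of power at HR 0.80 and 0.6 to 2.0 points at HR 0.75. For TXA bleeding it is 0.1 to 1.5 points, which is negligible.

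These sizes rest on three assumptions: the prognostic strength, for which the documents give no figure; the planned HR being read as marginal; and near-complete recording of the chosen covariates. The last is plausible because they are eligibility or TXA subgroup variables and every BP patient is also in the TXA trial, but the article does not state it.

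**What to change.** In Main analysis, pre-specify that the Cox model for the BP primary outcome, and for consistency the one for the TXA primary efficacy outcome, adjusts for a short list of baseline covariates. Suitable ones are age, surgery type, preoperative hemoglobin, eGFR, and history of coronary, peripheral arterial or cerebrovascular disease. Keep the planned stratification by the other factorial allocation. State that the adjusted HR is conditional on these covariates, and report the unadjusted HR beside it.

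Leave the non-inferiority decision against 1.125 on the planned model, because the margin and Table 3 were set without adjustment. An adjusted HR there can be supportive only.

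The cost is a few sentences and one extra model per outcome, with no new data. There are two downsides. The adjusted HR will differ slightly from the marginal HR behind the sample size (for BP at C = 0.75, about 0.788 against 0.80). A simple rule for missing covariate values must also be written down before unblinding.
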